**Child**				
	**Face-to-face school measures**			
		1 × 24-hour urine sample	✓	✓
		1 × overnight urine sample	✓	✓
		Weight, height, and waist circumference	✓	✓
		Taste-testing session	✓	✓
	**Online measures**			
		Australian Child and Adolescent Eating Survey (completed by parent proxy)	✓	
		Child salt survey to assess knowledge, attitudes, and behaviors	✓	
		Program evaluation questionnaire		✓
		Evaluation interview (subsample n=10)		✓
**Parent**				
		1 × 24-hour urine sample (optional)	✓	✓
		Parent salt survey to assess knowledge, attitudes, behaviors, and demographic characteristics	✓	✓
		Program evaluation questionnaire		✓
		Evaluation interview (subsample n=10)		✓
**Teachers/principals**				
		Evaluation interview		✓

#### Online Salt Survey (Parent)

The study parent will complete an online questionnaire, containing 34 questions (baseline) and 21 questions (postintervention) assessing sociodemographic characteristics such as age, sex, and education level (13 questions) and knowledge, attitudes, and behaviors related to salt intake. The survey was based on a previously validated salt knowledge questionnaire [62,64], while other questions were modelled on those used in past surveys [65-67], and was tested for readability in 5 parents from varying demographic backgrounds. The pre- and postintervention surveys for parents were identical, with the exception of excluding demographic information on the follow-up survey.

We included 14 knowledge questions assessing declarative (ie, relationship between salt and sodium, current recommendation, main sources, health conditions related to excessive salt intake) and procedural knowledge (interpreting sodium information on food labels). These question responses are in the form of multiple choice and 5-point Likert scale (“strongly disagree” to “strongly agree”). All correct responses will be scored as 1, while incorrect responses, including “don’t know” and “not sure,” will be scored as 0. Responses to Likert scale questions will be scored as a 2 for “certainly true,” 1 for “probably true,” and 0 for incorrect answers, including “not sure” and “don’t know” responses. Negative statements will be reversed prior to scoring. The salt knowledge questions will be summed to generate scores for each question, and a total salt knowledge score will be derived by summing all the knowledge questions. The minimum and maximum salt knowledge scores are 0 and 32, respectively. We added some additional questions assessing knowledge specific to salt consumption in children, as the original validated questionnaire was not directed to parents.

We assessed 3 attitude questions (ie, parents’ personal attitude toward their own salt intakes, salt as a flavor enhancer, taste of low-salt foods, and importance of reducing salt) using 5-point Likert scales (“strongly disagree” to “strongly agree”). Scores will be assigned from 1 (“strongly disagree”) to 5 (“strongly agree”). The scores will be summed to derive a total beliefs score. The minimum and maximum attitude scores will be 0 and 6, respectively, with a score of 3 assigned for “strongly agree,” 2 for “agree,” 1 for “neither agree nor disagree,” 0 for “disagree” or “strongly disagree.” Higher scores will indicate stronger beliefs about the importance of the salt in food for taste. Some questions regarding attitudes related to salt intake will be presented as percentages.

We assessed 4 behavior questions regarding discretionary salt use (ie, adding salt to food during cooking [parent] or at the table [child and parent], and placing a salt shaker on the table [child and parent]) using 5-point Likert scales. Scores will be assigned from 0 for “always” to 4 for “never.” Parents will report the frequency of current actions taken to reduce their child’s salt intake (and actions taken in the past 1 month in the follow-up survey) using a 7-point Likert scale. The scores will be summed to derive a total behaviors score according to frequency of engaging in behavior (6 for “never,” 4 for “2-3 times/week,” etc). The minimum and maximum behavior score will be 0-53, respectively. Higher scores will indicate a higher frequency in engaging in positive salt related behaviors.

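### The parent behaviour score gives its top code to never taking salt-reducing actions, against its stated direction, and its maximum of 53 cannot arise from its items

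*Protocol article*

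**What the plan says.** The section Online Salt Survey (Parent) of the Protocol article builds one parent behaviour total from two kinds of item.

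- **Discretionary salt use.** "We assessed 4 behavior questions regarding discretionary salt use", on 5-point scales. "Scores will be assigned from 0 for “always” to 4 for “never". A higher code means less salt added.
- **Salt-reducing actions.** "Parents will report the frequency of current actions taken to reduce their child’s salt intake", on a 7-point scale. The number of actions is not given. The codes are described as a "total behaviors score according to frequency of engaging in behavior (6 for “never,” 4 for “2-3 times/week,” etc".

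On the range it says: "The minimum and maximum behavior score will be 0-53, respectively". On the direction: "Higher scores will indicate a higher frequency in engaging in positive salt related behaviors".

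The action items ask about current actions at baseline "and actions taken in the past 1 month in the follow-up survey". Earlier in the same section: "The pre- and postintervention surveys for parents were identical, with the exception of excluding demographic information on the follow-up survey".

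The Data Analysis section models change in the parent survey scores, behaviour included, by multilevel regression. The Introduction places parent behaviour within the primary objective, beside the 20% reduction in the child's salt intake.

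**The concern.** The action items measure desirable behaviour, so a parent who never acts should score lowest. The printed rule gives that parent the highest code. The discretionary items run the right way, so the total adds components that point in opposite directions. The section mentions reversing items only for negatively worded knowledge statements and gives no such step for behaviour.

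The stated range might have shown which coding was intended, but it does not fit the described items under either direction.

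An analyst who follows the text would score uptake of the taught actions as a loss. A reader of the results could not tell what the sign of a reported change means. The change in recall period is a smaller, separate matter. It contradicts the statement that the two surveys match, and it could affect how comparable the action items are before and after the programme.

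**Working it through.** **Inputs, all from Online Salt Survey (Parent).** Discretionary items: a = 4, each scored 0 to 4. Action items: b, not stated. With seven points, a top code of 6 and a total minimum of 0, each action item runs 0 to 6. Stated maximum: 53.

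**Can b be recovered from the question counts?** At follow-up there are 21 questions, and 14 knowledge + 3 attitude + 4 behaviour = 21. Baseline less demographics gives the same: 34 - 13 = 21. The count leaves no separate room for action items, so b stays unknown.

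**Reproducing the stated maximum.** Maximum = 4a + 6b.

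- With a = 4: 53 - 16 = 37, and 37/6 = 6.17, which is not a whole number.
- In general 4a + 6b = 2(2a + 3b) is even, and 53 is odd. No numbers of items give 53.

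The bracketed list of discretionary behaviours could be read as 3 or 5 items, so the nearest reachable maxima are:

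| Discretionary items | Below 53 | Above 53 |
|---|---|---|
| 3 | 12 + 36 = 48 | 12 + 42 = 54 |
| 4 | 16 + 36 = 52 | 16 + 42 = 58 |
| 5 | 20 + 30 = 50 | 20 + 36 = 56 |

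Other codings were tried with 3, 4 or 5 discretionary items: 0-4 with 1-7, 1-5 with 0-6, 0-4 with 0-5, and 1-5 with 1-7. Only the last reaches 53, with five items of 1-5 and four of 1-7: 25 + 28 = 53. Its minimum is 5 + 4 = 9, which contradicts both the stated minimum of 0 and the printed 0-4 codes.

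**Direction, scored as printed.** A parent moves from never (6) to 2-3 times a week (4) on every action, so the change in the action part is b x (4 - 6). The values of b are assumptions.

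| Action items (b) | Action part | Plus one step better on all 4 discretionary items (+4) | Plus the full gain, 0 to 4, on all 4 (+16) |
|---|---|---|---|
| 5 | -10 | -6 | +6 |
| 6 | -12 | -8 | +4 |
| 7 | -14 | -10 | +2 |

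**Direction, aligned, with b = 6.** If only the code for never is wrong (never = 0, 2-3 times a week = 4), the same parent gains 6 x 4 = 24. If the whole printed scale is mirrored (6 minus the code: never = 0, 2-3 times a week = 2), the gain is 6 x 2 = 12.

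**Weight of the action items, with b = 6.** 36 of 52 points, or 69%.

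**The case against.** The strongest reply is that the code for never is a slip in a condensed article. The intended direction is stated outright, and a code of 4 for 2-3 times a week also fits a 7-step scale that rises with frequency. The instrument and full scoring key are not shown, and the key may be sound. This is plausible and stands as a limit: the documents do not show that any data have been scored backwards. But the two printed codes taken together fit a falling scale, so the slip reading requires changing one of them, and the stated range cannot settle which. The text still needs correcting.

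A reader might infer that any real improvement would appear as deterioration. The documents do not support that. The discretionary items are coded correctly, stopping use of the salt shaker is the first of the programme's three messages, and a full gain on those items outweighs the reversed action items (+2 to +6 above). The supportable statement is that improvement could be masked or reversed.

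A reader might also subtract 16 from 53 and conclude that 37 points, about 70% of the scale, are reversed. That uses a total that cannot occur. The true share depends on the unstated number of actions.

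Three further points stand. The wrong maximum does not enter the regression of change, so on its own it is a reporting error. The planned McNemar tests on individual responses do not depend on the summed codes, so a reversal might be noticed there. And a past-month frame after a 5-week programme is a reasonable way to tie the follow-up answers to the intervention period, so it gives no ground for dropping the action items.

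**Conclusion.** The point holds as a contradiction in the printed scoring rule. The code for the action items and the stated direction of the total cannot both be true, and 53 is unreachable for any number of items scored 0-4 and 0-6. If the rule is followed, uptake of the taught actions lowers the score: 12 points for a move from never to 2-3 times a week on six actions, where six is an assumption, or 10 to 14 points for five to seven actions. Improvement in parent behaviour could be masked or reversed.

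A reader might infer that the trial's main result is at risk. It is not. The Urine Collection section defines the primary outcome as change in the child's salt intake by 24-hour urine, and the sample size rests on that alone. The fault touches one modelled survey score, which is a component of the primary objective.

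The mismatch between current and past-month wording and the claim of identical surveys is real, but the documents give no basis for sizing its effect.

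**What to change.** Before the analysis is run:

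1. Check the survey codebook for the code attached to each response option of the action items.
2. Code those items from 0 for never to 6 for most frequent, so that all behaviour items point the same way.
3. State the number of action items and restate the maximum as 16 + 6 x that number (52 for six, 58 for seven).
4. Reconcile the current and past-month wording with the statement that the two surveys are identical. When change in the action items is reported, note the differing time frame.

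Consistent coding is enough to remove the contradiction. Separate sub-scores for the two kinds of item are optional. The cost is a recode in the analysis program and corrected wording, with no new data. The article reports that data were still being collated and cleaned, so the correction can precede the analysis.

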#### Taste-Testing Procedures

Tastings will be conducted with 2 commercially available food products, 1 snack food (potato chips) and 1 staple food (cornflakes), both of which are important sources of dietary salt for children [32]. We used the sodium content listed on packaged nutrient information panels to select 3 products of varying salt content for each food (Table 3). Nutrient profiles, particularly sugar and fat, were matched as closely as possible between samples of the same food type, as was visual appearance. Children will complete 2 taste tests for each food type during the testing session completed at schools (1) preference tests and (2) ability to rank samples according to salt content.

**Table 3 table3:** Sodium content of chip and cornflake samples.

Food products		Sodium (mg/100 g)	Salt equivalent (g/100 g)
**Chips**			
	No added salt	14	0.04
	Mid salt	200	0.5
	High salt	486	1.2
**Cornflakes**			
	Low salt	90	0.2
	Mid salt	390	1.0
	High salt	590	1.5

All samples of chips and cornflakes will be presented in plain containers in a predetermined randomized sequence. Children will be asked to have a drink of water between tasting each food sample. On completion of tasting the 3 samples, children will be asked which one they liked the most (ie, preference). The most liked sample will be removed from sight and the question repeated for the remaining 2 food samples. This forced-choice rank-order method means that each child will rank the 3 samples from most to least preferred. Following the same procedure, the child will then be asked which sample they think tastes the saltiest (ie, ability to rank samples). This rank-order method is based on previous methods [68] and has been successfully used in a similar sample of children ranking sour intensities and preference [69].

### Data Analysis

We will use Stata SE 14 (StataCorp LP) for all statistical analyses. Descriptive statistics will describe continuous (mean, SD) and categorical (n, %) measures. McNemar test will assess the change in proportion of responses in the pretest and posttest surveys. Multilevel regression models will assess the change in salt intake among children, as well as child and parent salt survey scores (knowledge, attitudes, and behaviors). Models will adjust for potential confounders (ie, age, sex, and parental level of education). To assess whether participation in the program alters salt preference, we will group participants based on the sample they most preferred, and we will use the McNemar test to assess the change in proportion of children’s preferences before and after the intervention. Statistical significance will be set at *P*<.05.

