Past evidence indicated that educational messages targeting the key sources of salt in the diet [17] and behavioral skills, such as reading food labels to select lower-salt foods [18] or using herbs and spices instead of salt to flavor food [19], are key components of effective programs to reduce salt intake in adults. However, there is little evidence of effective behavioral-based strategies for reducing salt intake in schoolchildren. The expansion of Internet technologies within the home in Australia [20] provides an important opportunity to deliver public health interventions. In 2014-2015, 97% of Australian households with children aged under 15 years had access to the Internet [20]. Although there is a social gradient for Internet access in Australia, access among more marginalized groups is still relatively common (eg, 77% of those educated to grade 12 or below have Internet access) [20]. Research suggests that online technologies can be used to engage children to achieve positive changes in dietary behaviors [21,22], for example, improved intakes of fruit and vegetables [23]. To date, no Web-based behavioral intervention targeting salt reduction in Australian schoolchildren has been trialed. Hence, we sought to develop and pilot test a Web-based salt-reduction program that targets primary school children and their parents. The primary objective of the program is to reduce salt intake among children by 20% and improve child and parent knowledge, attitudes, and behaviors related to salt intake. Secondary objectives relate to taste preferences in children; these include (1) assessing their salt preference for commercially available foods of varying salt concentration, (2) assessing the association between salt preference and salt intake, and (3) assessing whether participation in the program alters salt preference.

The purpose of this paper is to describe the Digital Education to Limit Salt Intake in the Home (DELISH) program and data collection methods that we will use in the study. In addition, we report on findings related to the development of the program, which includes pilot testing of educational materials among a sample of children aged 8-12 years.

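### McNemar is named for a three-level preference grouping, with no dichotomy or multi-category extension stated, so the test does not match the grouping or use the salt order

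*Protocol article*

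**What the plan says.** The Introduction lists, as the third secondary objective on taste, "assessing whether participation in the program alters salt preference". Under Taste-Testing Procedures, "Tastings will be conducted with 2 commercially available food products" (potato chips and cornflakes), and label sodium was used to "select 3 products of varying salt content for each food". Table 3 gives 14, 200 and 486 mg of sodium per 100 g for the chips and 90, 390 and 590 mg per 100 g for the cornflakes. The forced-choice procedure means that "each child will rank the 3 samples from most to least preferred". Table 2 places the "Taste-testing session" at both baseline and postintervention.

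For analysis, the Data Analysis section says "we will group participants based on the sample they most preferred, and we will use the McNemar test", and applies that test to the change in preference proportions between the two occasions. Significance is set at P<.05. The article does not say how three groups become two, which proportion is tested, or whether a version of the test for more than two categories is meant.

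**The concern.** The grouping and the test are both stated, and they do not fit each other. A child's most preferred sample of a food has three possible values, and McNemar's test is for a paired response with two. To carry out the sentence, the analyst must add a step that the article does not give: choose one split, run several splits, or substitute another test.

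This is the only test assigned to the objective on change in preference. The three possible splits answer different questions and can differ greatly in power, so the unstated step could decide the conclusion. The objective concerns salt and the samples are graded by salt, yet the test as named makes no use of that order.

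**Working it through.** The protocol gives no sample size, effect or power for the preference comparison, so there is no figure to reproduce. The check is structural, followed by an illustration of size.

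**Structure, per food**
- Let n_ij be the number of children preferring sample i before and sample j after, with i and j in {low, mid, high}.
- The table has 3 × 3 = 9 cells, of which 9 − 3 = 6 are discordant.
- McNemar's statistic is (b − c)²/(b + c) on 1 df, where b and c are the two discordant cells of a 2 × 2 table. It is not defined on the 3 × 3 table.
- One sample against the other two gives a usable b (children leaving that sample) and c (children moving to it). There are 3 such splits per food, hence 6 over two foods.
- Paired tests that take the whole table exist: Stuart-Maxwell (equal margins, 2 df), Bowker (symmetry, 3 df), and a 1-df test on the change in salt level scored 0, 1, 2. Only the last uses the salt order.

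**Illustration: assumed inputs, none from the documents**
- Baseline shares 20/30/50% for low/mid/high; underlying normal preference with within-child correlation 0.5; two-sided 0.05.
- n = 98, being 122 × 0.8 = 97.6 rounded up. The protocol's 20% covers dropout or incomplete urine samples, and an incomplete urine sample need not remove a child's taste data, so 98 is itself an assumption.
- A shift of 0.35 SD towards less salt gives postintervention shares of Φ(−0.842 + 0.35) = 31% low, 1 − Φ(0.35) = 36% high, and the remaining 33% mid. The middle share hardly moves (30% to 33%), which is why its split has almost no power.

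| Simulated rejection rate | No change | Shift 0.35 SD |
|---|---|---|
| McNemar, low v rest | about 0.05 | 0.58 |
| McNemar, mid v rest | about 0.05 | 0.06–0.07 |
| McNemar, high v rest | about 0.05 | 0.65 |
| Stuart-Maxwell | about 0.05 | 0.69 |
| Paired ordinal test | about 0.05 | 0.79 |

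Under no change, the chance that at least one of the three splits reaches P<.05 is about 12% per food. The value for three independent tests is 1 − 0.95³ = 14.3%; the splits share children and cells, so the simulated figure is lower.

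**Second set of assumptions.** With 102 children and shares moving from 21/32/47% to 33/35/32%, power was 0.70, 0.08 and 0.81 for McNemar on low, mid and high, 0.75 for Bowker, 0.82 for Stuart-Maxwell and 0.90 for the ordinal test. The pattern is the same.

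**The case against.** The strongest reply is that McNemar becomes valid once one split is fixed, for example the highest-salt sample against the other two. Such a split also uses part of the salt order. The wording about a change in proportion fits that reading, or a loosely named extension such as McNemar-Bowker, and a condensed article may leave the detail to a fuller plan. The first part stands: the test can be adapted, and the defect is a mismatch in what is written. The appeal to condensation does not dispose of the point, because the article does state both the grouping and the test, and the two disagree.

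The power argument also has limits. High-v-rest McNemar is about level with Stuart-Maxwell (0.39 each at a 0.25 SD shift; 0.65 against 0.69 at 0.35 SD). The clear gain comes from scoring the order, and the simulated shift was itself monotone in salt.

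Three stronger readings are tempting but unsupported.
- A reader might infer that the false-positive rate is inflated as planned. The article names a single McNemar test and does not propose running every split and counting any success. The 12% describes only that possible route, and a figure over both foods would further require the foods to be independent although the same children rate both.
- A reader might infer that the cut would be chosen after seeing the data. The article does not say when it would be chosen.
- A reader might infer that the full ranking is wasted. The ranks may serve the other taste objectives, and the remedy below also uses only the most preferred sample.

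**Conclusion.** The point holds as a mismatch: a test for paired binary data is assigned to a three-level grouping, with no dichotomy or extension given, and the salt order goes unused. That conclusion follows from the text and needs no simulation.

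Its size is only illustrative. Under the assumed 20/30/50% shares, correlation 0.5 and 98 children, the choice of split moves power between about 0.06 and 0.65 at a 0.35 SD shift, against about 0.79 for an ordinal test. Other shares or shifts would change these values.

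It should be fixed, but it is not critical. It touches one secondary objective in a single-arm pre-post study whose Discussion already concedes that changes may have other causes. The primary outcome, change in 24-hour urinary sodium, is analysed with multilevel models and is unaffected.

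**What to change.** Replace the McNemar sentence for preference with one prespecified paired test per food on the three-level salt category of the most preferred sample. Suitable choices are:
- a Wilcoxon signed-rank test on the ordered salt level;
- an ordinal mixed model with time as the effect, which can also carry school clustering; or
- the Stuart-Maxwell test of marginal homogeneity, if the categories are to be treated as nominal.

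The minimum alternative is to state one dichotomy per food, such as the highest-salt sample against the other two, and keep McNemar. That is valid, but it uses only part of the order and had less power than the ordinal test in the illustration.

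The cost is one sentence in the analysis section, settled before the preference data are analysed. No new data are needed.
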